### Dissemination plan

The main findings will be published in the subsequent registered report article. Given the multisite nature of this study, individual sites may choose to develop their own specific hypotheses that extend beyond this protocol, and may choose to develop additional outputs beyond the associated registered report article. The SingWell Project is also committed to knowledge mobilization activities involving key stakeholders such as choirs, physicians, hearing health professionals, and community centres. Full details can be found on their website (https://www.singwell.ca/) and from the SingWell Project protocol [88].

## Data analysis

### Statistical power analysis

An a priori power analysis was conducted to determine the sample size needed to detect the smallest effect size of interest. We determined the number of participants needed to detect the cross-level interaction of group (i.e., group singing vs. audiobook club) and time (i.e., *baseline* vs. *completion*) on SIN perception. The power analysis was conducted using traditional approaches where the resulting sample size refers to the level 2 clusters–in this case, the number of participants.

*G*Power* version 3.1.9.4 was used to conduct the analysis for an ANOVA within-between factor interaction [119]. For a conservative estimate, we assumed a small effect size of, η^2^ = .01, corresponding to an effect size of f = 0.1. We estimated the correlation among the repeated measures to be *r* = .62, based on a previous group-singing controlled trial that reported an intraclass correlation (ICC) of .62 [64]. Accounting for a 20% attrition rate [64], the power analysis (f = .10, *α* = .05, *r* = .62) suggests a total sample size of *N* = 206 participants, approximately *n* = 30 per site for 85% power.

In addition to the power analysis, we also calculated the reliability of our repeated measurements to assess for sufficient reliability for each participant based on [120] (1):

$$n_{min}=\frac{\rho (1-ICC)}{\left(1-\rho )(ICC\right)}$$
(1)

where *n* min is the number of time points and *ρ* is the population correlation across all the timepoints. Given our two timepoints and estimated ICC of .62, we have adequate-to-good reliability of our timepoints, *ρ* = .77.

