### Participants

Participants will be recruited from seven sites around the world: Toronto, Montreal, and St John’s (Canada); Los Angeles (United States of America); Groningen (Netherlands); Oldenburg (Germany); and Adelaide (Australia). Each site will aim to recruit a total of 30 participants with a simple randomisation using a 1:1 computer generated allocation (15 randomly assigned to group singing, and 15 randomly assigned to the audiobook club), for a total of 210 participants among all the sites. Participants will not be able to change their allocation.

Recruitment will be variable as each site will have access to different databases, networks, and communities. Hence, recruitment flyers will be sent to a range of organisations such as: deaf and hard-of-hearing organisations, aged-care homes/retirement centres, senior centres, veterans organisations; and to databases such as the Toronto Metropolitan University Auditory Participant Pool and the Toronto Metro Senior Participant Pool. To avoid potential participant bias, flyers will advertise that the study is looking for participants to engage in a creative group activity, rather than group singing or an audiobook club, specifically.

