For each micro-level dependent variable, three separate MLMs will be defined: 1) an intercept-only model; 2) a main-effect only model (DV_change_ ~ *group + time*) and 3) an interaction (DV_change_ ~ *group * time*) model. For micro-level models, the time variable will reflect the time point of the micro-level observation and will allow us to model changes between the group across time. Similarly, three separate MLMs will be defined for macro-level dependent variables: 1) an intercept-only model; 2) a main-effect only model (DV ~ *group + session*) and 3) an interaction (DV ~ *group * session*) model. For both macro and micro-level models we will use a hierarchical modeling technique to determine which model is the best fit to the data. Model fit parameters will be compared between the three models and results of the model with the best fit will be reported on. Upon the discovery of a significant interaction, a follow-up simple slope analysis will be used to examine the differences in time (e.g., *baseline* vs. *completion*) across groups. For all hypothesis tests, alpha values will be set at 0.05.

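### Under the ANOVA used for sizing, 85% power with 20% attrition needs 215 to 218 enrolled, not 206; the shortfall is minor

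*Protocol article*

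**What the plan says.** The section Statistical power analysis sizes the trial on "the cross-level interaction of group (i.e., group singing vs. audiobook club) and time" for speech-in-noise perception, from baseline to completion. G*Power "was used to conduct the analysis for an ANOVA within-between factor interaction". The effect is eta squared = .01, "corresponding to an effect size of f = 0.1". The correlation between repeated measures is .62, "based on a previous group-singing controlled trial that reported an intraclass correlation (ICC) of .62". Alpha is .05, and the section Modelling and inferential statistics agrees: "For all hypothesis tests, alpha values will be set at 0.05".

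The result is introduced with "Accounting for a 20% attrition rate [64], the power analysis" and given as N = 206 in total, about "30 per site for 85% power". The section Participants rounds this to seven sites of 30, "for a total of 210 participants among all the sites". Neither section gives the number of completers required or the way the 20% was applied.

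**The concern.** A loss of 20% leaves 80% of those enrolled, so the number required at completion has to be divided by 0.8. Multiplying it by 1.2 covers a loss of only one sixth (1 - 1/1.2 = 16.7%). The printed 206 looks like the product of the second operation. If so, the 85% power statement does not hold at the attrition rate it claims to have absorbed. The article offers its powered sample as an answer to the small studies that came before, so the figure ought to follow from its own inputs.

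**Working it through.** **Inputs**, all from the Protocol article: 2 groups with 1:1 allocation, m = 2 time points, f = .10 (or eta squared = .01), alpha = .05, r = .62, power 85%, attrition 20%, 210 planned. Participants are treated as independent, as in the article's own calculation.

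**Effect size.** Eta squared = .01 converts exactly to f = sqrt(.01/.99) = .1005; the article rounds this to .10. Both values are carried through.

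**Method.** For the within-between interaction, the noncentrality is lambda = f² x N x m/(1 - r), with an F test on 1 and N - 2 degrees of freedom.

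**Completers needed for 85% power** (even totals, equal arms):
- f = .1005: N = 172, lambda = .010101 x 172 x 2/.38 = 9.14, power 85.2%.
- f = .10: N = 174, lambda = .01 x 174 x 2/.38 = 9.16, power 85.3%. At 172 the power is 84.9%.

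**Reproducing the stated 206.**
- With no attrition, 206 would have 90.6% power at f = .10, so 206 is not the uninflated figure.
- 172 x 1.2 = 206.4, which matches. 174 x 1.2 = 208.8, which is close but not 206.
- 172/0.8 = 215 and 174/0.8 = 217.5, i.e. 218. Neither is 206.
- Division by 0.8 comes near 206 only with alpha .10 and 90% power (166/0.8 = 207.5), which contradicts the stated alpha and power.

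**Power left after 20% loss, same ANOVA:**

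| Enrolled | Completers | Power, f = .10 | Power, f = .1005 |
|---|---|---|---|
| 206 | 164.8 | 83.3% | 83.7% |
| 210 | 168 | 84.0% | 84.4% |

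The shortfall in enrolment is 9 to 12 participants from 206, and 5 to 8 from 210.

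**Attrition that 210 can bear at 85% power:** 1 - 174/210 = 17.1% to 1 - 172/210 = 18.1%.

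**The planned model.** The macro analysis is a group-by-session mixed model with a random intercept per participant, so a dropout's baseline score is kept. With c completers out of N and unit variance, the variance of an arm's estimated change is:
- completers only: 2(1 - r)/c = .76/c
- with dropouts' baselines: (1 - r²)/c + (1 - r)²/N. At c = .8N this is (.6156 + .1444 x .8)/c = .7311/c

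The ratio is .76/.7311 = 1.0395, a gain of about 4%. The effective number of completers is 164.8 x 1.0395 = 171.3 at 206 enrolled, and 168 x 1.0395 = 174.6 at 210. Power is then 84.7 to 85.1% at 206 and 85.4 to 85.8% at 210. This assumes that all dropouts have a baseline score, that data are missing at random, and that the variance components are known.

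**The case against.** The strongest reply is that the ANOVA is only a sizing device. The planned analysis is a mixed model, chosen partly because it tolerates missing data, and baseline testing takes place before training starts. A reader might infer that a participant lost before completion contributes nothing to the contrast, and so that 210 cannot deliver 85%. The documents do not support that. It is true of an ANOVA or of change scores on completers, but in the planned model the baseline score of a dropout carries information through r = .62. This part of the reply stands, and under the assumptions above 210 reaches 85%. It does not rescue the stated derivation, which reports an ANOVA total plus an attrition allowance and takes no credit for partial data. The model-based figure also leaves out any values removed by the planned boxplot rule for outliers.

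Second, the multiplication by 1.2 is an inference. No formula is printed, and the printed f = .10 gives 208.8; the exact match needs f = .1005. That also stands. The shortfall does not depend on it, because 80% of 206 and 80% of 210 both fall below 172.

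Third, the effect is small against the uncertainty in r and in the attrition rate, both taken from a single earlier study. That is fair, and it limits the weight of the point.

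**Conclusion.** The stated N = 206 does not follow from its stated inputs. Under the completer-based ANOVA that the article reports, 20% attrition requires 215 to 218 enrolled. At 20% loss, power falls short of 85% by 1.3 to 1.7 points with 206 enrolled and by 0.6 to 1.0 points with the planned 210. The calculation is firm for that method; the explanation by 172 x 1.2 is likely but inferred.

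A reader might go further and conclude that the trial is materially underpowered or has to recruit more. Neither follows. The gap at the actual target is at most one point under the sizing method, and it may vanish under the planned mixed model. This is a minor error in a reported figure.

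**What to change.** In Statistical power analysis, state that 85% power requires about 172 to 174 completers, say how attrition was applied, and delete N = 206. Then report the power of 210 enrolled in one of two ways:

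- Under the completer ANOVA: about 84% power at 20% attrition, with 85% power holding up to about 17 to 18% attrition.
- Under the planned mixed model, if the sponsor prefers to rely on it: about 85.4 to 85.8% power at 20% attrition, with the assumptions stated (every dropout has a baseline score, data missing at random).

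The cost is a sentence or two. Recruitment, conduct and analysis are unchanged. Under the first option the stated power becomes about one point less favourable.

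### The effect called small and conservative in the power analysis is a 0.40 SD between-arm difference in change; the attrition inflation also looks slightly short

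*Protocol article*

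**What the plan says.** All of this is in the protocol article. Under *Statistical power analysis*, the calculation is meant to "determine the sample size needed to detect the smallest effect size of interest". The target is to "detect the cross-level interaction of group (i.e., group singing vs. audiobook club) and time", from baseline to completion, on speech-in-noise perception. G*Power "was used to conduct the analysis for an ANOVA within-between factor interaction". The effect is set as follows: "For a conservative estimate, we assumed a small effect size of, η^2^ = .01, corresponding to an effect size of f = 0.1". The other inputs are α = .05, a correlation of .62 between repeated measures, and 20% attrition, and the result "suggests a total sample size of *N* = 206 participants, approximately *n* = 30 per site for 85% power".

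The section gives neither the number needed before attrition nor the inflation formula. It does not express the effect in SD units or in dB of speech reception threshold.

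Under *Participants*, seven sites each recruit 30 people, 15 per arm, "for a total of 210 participants among all the sites". Under *Modelling and inferential statistics*, the analysis is a linear mixed model, described as suited to missing data.

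**The concern.** Cohen's f is a familiar scale for a one-way comparison, where 0.10 is conventionally small. In a 2 × 2 within-between interaction it is easy to misread. The default G*Power routine scales f to the SD of a single measurement and then gains precision from the correlation between measurements. The treatment contrast of interest, the difference between arms in change, is a multiple of f and not f itself. A label that suits f may therefore not suit the contrast being tested.

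At stake is what a null speech-in-noise result could support. A reader told that the trial was sized for the smallest effect of interest would take a non-significant result as evidence against modest benefits. That inference is sound only if power for modest benefits is high. Separately, the stated N does not look like the usual division by the retention fraction.

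**Working it through.** **Inputs** (*Statistical power analysis*, *Participants*): two arms, two time points, f = 0.10 (or √(.01/.99) = 0.1005 if converted exactly from η² = .01), α = .05, r = .62, 85% power, 20% attrition, 210 to be randomised.

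**1. Reproduce the stated N.** For the default within-between interaction, the noncentrality is λ = f² × N × 2 / (1 − r), with 1 and N − 2 degrees of freedom.

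- With f = 0.1005, 85% power is reached at 171 (172 if N is even, power 85.2%).
- With f = 0.10, it is reached at 173 (174 if even); 172 gives 84.9%.
- 172 × 1.2 = 206.4, which matches 206. 172 / 0.8 = 215. At exactly f = 0.10, division gives 173 / 0.8 = 216.25, so 217, or 174 / 0.8 = 217.5, so 218.

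Targets of 80% and 90% power at r = .62 did not give 206 with either inflation. The routine is therefore identified with fair confidence. The multiplier of 1.2 is an inference.

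**2. Translate f into the treatment contrast.** In a 2 × 2 interaction, f = 0.10 puts each cell ±0.10 outcome SD from its additive expectation.

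- Difference in change between arms = (0.10 + 0.10) − (−0.10 − 0.10) = 4 × 0.10 = 0.40 outcome SD.
- SD of change = √(2 × (1 − .62)) = √0.76 = 0.872 outcome SD.
- Standardised difference in change scores = 0.40 / 0.872 = 0.46.
- λ / N = 0.01 × 2 / 0.38 = 0.0526, so interaction partial η² = 0.0526 / 1.0526 = .05.

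As a cross-check, a two-sample comparison of change scores with difference 0.40 and SD 0.872 needs 86 per arm, or 172 in total.

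**3. Power with 168 completers (210 × 0.8), before clustering.**

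| Difference in change (outcome SD) | f | Power |
|---|---|---|
| 0.40 | 0.10 | 84% |
| 0.30 | 0.075 | 60% |
| 0.20 | 0.05 | 32% |

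For 85% power at 0.20 SD, 686 completers would be needed (686 / 0.8 = 857.5, so 858 randomised).

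**4. Cost of the inflation.** Completers only, f = 0.10: 206 leaves 164 (83.2%) and 210 leaves 168 (84.0%).

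Under a mixed model that keeps participants with only a baseline value, assume that all loss follows baseline testing and that data are missing at random. The variance of an arm's mean change is then proportional to (1 − r²)/n_completers + (1 − r)²/n_randomised, against 2(1 − r)/n_completers for completers only. Since completers are 0.8 of those randomised, multiplying through by n_completers gives 0.6156 + 0.1444 × 0.8 = 0.7311 against 0.76, a gain of 4%. At 210 randomised this is worth about 174.6 completers, or about 85% power. At 206 it is worth about 171, or 84.7%.

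**5. Clustering, illustration only.** Assume one training group per arm per site (14 groups), 12 completers in each, and design effect 1 + 11 × ICC. The article gives no ICC. Power for 0.40 SD:

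| Assumed ICC | Design effect | 12 df | 166 df |
|---|---|---|---|
| .02 | 1.22 | 70% | 76% |
| .05 | 1.55 | 59% | 66% |

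**The case against.** **Small is defined by η² and f, and on that definition the trial is adequately powered.** This is right. A reader might infer that 85% power for a small effect is simply not delivered. The article does not support that: its own definition is f = 0.10, and at f = 0.10 power is 83–85%. The shortfall appears only if small is taken to mean about 0.20 SD in change, which the article does not say. What remains is that f = 0.10 in this routine is a 0.40 SD contrast, and the text gives the reader no means of seeing that.

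**An interaction partial η² of .01 would need about 900 completers, with about 25% power at 168.** The arithmetic is correct, but that is a different effect-size specification from the one that yields 206. It shows that the bare η² is ambiguous, not that the stated N is wrong by that amount.

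**The attrition slip is inferred and trivial.** Both parts stand. The formula is not printed, 172 reaches 85% only with the unrounded f, and the planned mixed model recovers most of the loss. It is worth correcting but carries no weight of its own.

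**Clustered power figures rest on assumptions.** Also right. The ICC, the 14 groups and the degrees of freedom are all assumed, so no single figure should be presented as the trial's power.

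**The aim is exploratory, and nothing says a null result would exclude small benefits.** This is true of the article. But it does say that the sample was sized for the smallest effect of interest, and that statement invites the inference.

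**Conclusion.** The labels are wrong for the effect used. The trial is sized for a 0.40 outcome-SD difference in change between arms (0.46 SD of change, interaction partial η² about .05), with about 84% power among 168 completers and about 85% under the planned mixed model. Power falls to about 60% at 0.30 SD and 32% at 0.20 SD. Nothing in the section justifies 0.40 SD as the smallest difference worth detecting. A null result would therefore say little about benefits of 0.20 to 0.30 SD.

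The inflation is probably short by 9 participants at 206 (215 − 206) and by 5 to 8 at 210. It is a minor correction that does not affect the trial's viability.

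The conclusions rest on r = .62, on the default G*Power routine being the one used (it reproduces the N) and on no clustering. The mixed-model figure also needs loss to follow baseline testing and data to be missing at random.

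**What to change.** Keep N = 210 and rewrite the paragraph:

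- State: *210 randomised and 168 expected completers give about 84% power (completers only; about 85% under the mixed model), before any clustering by training group, for a between-arm difference in change of 0.40 outcome SD (interaction partial η² about .05).*
- Give that difference in dB of speech reception threshold, with the SD used for the conversion, and either justify it as the smallest effect of interest or drop that claim.
- Remove the words conservative and small.
- Show the attrition step as N / (1 − 0.20), with the number before inflation.
- Optionally, tabulate power over a range of assumed training-group ICCs, stating the group size and degrees of freedom.

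The cost is one paragraph and less favourable wording. No extra participants and no change to the design or analysis are needed.

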### Planned statistical analyses

#### Tests of equivalence

Given the sample size and random assignment to group, we assume that covariates such as age, gender, education, musical training/background, credibility, and expectation will be evenly distributed across the participants. Thus, we expect equivalence between participants and their randomly assigned intervention. To test this assumption, we will use a well-known technique to test for equivalence, the Bayesian *t*-test [121, 122]. Each Bayesian *t*-test will produce a coefficient called the Bayes Factor (BF), a measure of the likelihood of the alternative hypothesis (i.e., that the two samples differ). BF of 1 or less, will be interpreted as strong evidence for the null hypothesis [123]. Upon discovery of a BF larger than 1 we will conclude that the groups are not equivalent on this variable, and this variable will be used as a covariant in subsequently modeling of measures of interest.

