**Fig 1 pone.0314473.g001:**
[figure not shown]
Overview of the study design.

The rationale for the use of an audiobook club as a suitable control group is due to several factors. Firstly, listening to audiobooks is a common clinical recommendation for hearing loss and have been used in other RCTs as a control [89, 90]. Secondly, discussion from the audiobook club will generate asynchronous speech, which is a suitable compliment to investigate the targeted benefits of synchronized group singing. Finally, we anticipate that the credibility and expectation between both interventions will be similar given they are both group activities in the auditory domain.

This study was registered as a clinical trial (clinicaltrials.gov, U.S. National Library of Medicine, ID: NCT06580847); and adheres to a Standard Protocol Items: Recommendations for Interventional Trials (SPIRIT) Checklist with 2022 extension [91–93], which is provided in S2 Appendix. Any modifications to the protocol will require approval from the Toronto Metropolitan Research Ethics Board and will be noted in the subsequent registered report article.

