#### Demographics, social networks, musical background, credibility, and expectation

Participants will be asked to provide their demographic details such as age, sex, gender, residential status, and education. We will also measure their social network diversity (e.g., connections with friend, families, neighbours, etc.) with a subscale from the Social Network Index [97]. Participant’s previous musical training will be measured using the Musical Training subscale from the Goldsmith’s Musical Sophistication Index (Gold-MSI) [98]. This 7-item questionnaire captures the participants’ history of formal musical training with more points representing more musical training. Participant perspectives on the credibility and expectations in respect to their assigned group will also be recorded with the credibility/expectancy questionnaire [99].

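### A Bayes factor of 1 is neutral, yet the plan reads it as strong evidence of balance and uses it to choose covariates, including ratings made in respect to the assigned arm

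*Protocol article*

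**What the plan says.** In the protocol article, Data analysis, Tests of equivalence, the argument starts from sample size and random assignment: "we assume that covariates such as age, gender, education, musical training/background, credibility, and expectation will be evenly distributed". Bayesian t-tests are to check this. The Bayes factor is described as "a measure of the likelihood of the alternative hypothesis (i.e., that the two samples differ" (closing bracket omitted), so larger values speak for a difference. Two decision rules follow:

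- "BF of 1 or less, will be interpreted as strong evidence for the null hypothesis".
- "Upon discovery of a BF larger than 1 we will conclude that the groups are not equivalent on this variable", in which case "this variable will be used as a covariant in subsequently modeling of measures of interest".

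Two other places bear on the variables screened. The test-battery section that covers demographics and credibility says: "Participant perspectives on the credibility and expectations in respect to their assigned group will also be recorded". The rationale for the control arm, under Study design, says only that "we anticipate that the credibility and expectation between both interventions will be similar". The Background of the Abstract presents the statistical analysis as robust and planned beforehand.

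**The concern.** There are three linked problems.

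1. The label attached to the cut-off is wrong. A Bayes factor of 1 leaves the prior odds where they were. The plan would report strong evidence of balance where the data are neutral, or even where they show a moderate imbalance.
2. The same cut-off decides which covariates enter the outcome models. Selection then follows the imbalance that happens to be observed, not how well a variable predicts the outcome. That sits badly with an analysis described as planned in advance.
3. Credibility and expectation are screened as if they were baseline characteristics. They are ratings of an allocation that the participant already knows. Randomisation gives no assurance that they are balanced, and where they enter a model that estimates the arm effect, the result is conditional on something that allocation may have affected.

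**Working it through.** **Inputs from the protocol article.** The cut-off is a Bayes factor (BF) of 1, in the direction alternative over null (BF10). There are 210 participants allocated 1:1 by simple randomisation, so about 105 per arm. Six variables are named for screening, in a list introduced as examples, so six is a minimum.

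**Assumption.** The article gives no prior. I take a zero-centred Cauchy prior on the standardised difference, with scale r from 0.5 to 1.414 and 0.707 as the central case.

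**Step 1: what a BF of 1 means.** At equal prior odds, P(H0) = 1/(1 + BF10). For BF10 = 1 this is 1/2 = 0.50. For comparison, BF10 = 1/3 gives 0.75 and BF10 = 1/10 gives 0.91. That a BF of 1 is neutral does not depend on the prior scale.

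**Step 2: where the cut-off falls.** With N_e = 105 × 105/210 = 52.5 and ν = 208,

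BF10 = ∫ (1 + N_e g r²)^(−1/2) [1 + t²/((1 + N_e g r²)ν)]^(−(ν+1)/2) (2π)^(−1/2) g^(−3/2) e^(−1/(2g)) dg ÷ (1 + t²/ν)^(−(ν+1)/2).

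I solved this for the |t| at which BF10 = 1, took its two-sided p-value, and converted it to an observed difference d = |t|√(2/105). The chance that at least one of six truly balanced, independent variables exceeds the cut-off is 1 − (1 − p)^6.

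| Prior scale | t at BF10 = 1 | p | d (SD) | BF10 if means are identical | Any of six flagged |
|---|---|---|---|---|---|
| 0.5 | 1.884 | 0.061 | 0.260 | 0.206 | 31% |
| 0.707 | 2.015 | 0.045 | 0.278 | 0.150 | 24% |
| 1 | 2.153 | 0.0325 | 0.297 | 0.108 | 18% |
| 1.414 | 2.293 | 0.023 | 0.316 | 0.077 | 13% |

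Central case: 2.015 × √(2/105) = 0.278, and 1 − (1 − 0.0452)^6 = 0.242.

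**Step 3: how often a real difference gets the label.** At scale 0.707, a true difference of 0.3 SD falls at or below the cut-off 44% of the time, and one of 0.2 SD 71% of the time.

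**Step 4: credibility and expectation in the two kinds of model.** Let G be arm, S session and C a covariate that is constant over time.

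- *Micro level.* The outcome is already a pre-to-post change, and the planned model is change ~ group * time, so the group term carries the arm effect. If C adds b·C to the model, the group coefficient without C equals the coefficient with C plus b × (arm difference in mean C). If expectancy is higher in one arm and predicts larger change, adjustment removes that product from the arm effect. The article does not supply its size.
- *Macro level, C as a main effect.* With Y = b0 + b1G + b2S + b3GS + b4C + u + e, a participant's change is b2 + b3G + (e2 − e1). C and the participant effect u cancel. With complete data the interaction estimate is the difference in mean change, with or without C.
- *Macro level, C also interacting with session.* The change then contains b5C, so b3 becomes conditional on C and the micro-level argument applies. The article does not say in which form a flagged variable would enter.

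**The case against.** The strongest reply concerns the main contrast. Under Statistical power analysis the trial is sized on the group-by-time interaction for speech-in-noise perception, and the macro models estimate that interaction with a participant random intercept. A stable covariate entered as a main effect drops out of it. This stands, and it rules out several stronger readings that a reader might infer:

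- *That an unflagged imbalance biases the main result.* An imbalance of 0.27 SD in a covariate correlated 0.3 to 0.5 with the outcome gives 0.27 × 0.3 = 0.08 to 0.27 × 0.5 = 0.14 SD. That shift belongs to a comparison of arms at a single timepoint, which the article does not plan for the macro outcomes. A simulation with 105 per arm, that imbalance, covariate-outcome correlation of about 0.5, repeated-measures correlation 0.62 and a true interaction of 0.40 gave 0.402 both unadjusted and adjusted. With 20% random dropout it gave 0.405 both ways.
- *That fixed covariates would always gain precision.* In the same simulation the interaction's standard error was 0.121 with and without the covariate, and 0.132 against 0.131 with dropout.
- *That adjusting for expectancy removes part of the main macro effect.* It does so only if the covariate also interacts with session.
- *That a BF10 below 0.10 is unattainable at this sample size.* This holds in the table for scales up to 1, but at 1.414 the minimum is 0.077.

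On credibility and expectancy, the article gives no timing for the questionnaire. If it is completed before the first session, the sessions cannot have changed the ratings, and adjusting for unequal expectancy can be a deliberate choice about which effect to estimate. That is fair, so I do not say that the sessions alter them. It is enough that the ratings concern a known assignment. The article's reason for expecting balance is random assignment, and that reason does not cover such a variable.

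The article cites a source for its reading of the BF, which is not at hand. No source is needed to see that a ratio of 1 is neutral.

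**Conclusion.** The rule is wrong as written. Reading a BF of 1 or less as strong evidence for the null contradicts the section's own definition of the factor under any prior. In practice the rule is close to a baseline significance test at p of about 0.06 to 0.02. It would call observed imbalances up to about 0.26 to 0.32 SD strongly equivalent, and by chance alone it would change the covariate set 13% to 31% of the time.

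These figures rest on about 105 per arm, the assumed range of Cauchy scales and, for the last one, six independent variables tested as if continuous, which suits gender and education poorly. Including credibility and expectation is a real weakness for the micro-level models, and for the macro models if they interact with session. Its size cannot be derived from the article. No bias and no general gain in precision is claimed for the powered macro interaction. The point should be corrected, but it does not undermine the trial's main contrast.

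**What to change.** In Tests of equivalence:

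- Delete the strong-evidence reading and the rule that turns a BF above 1 into a covariate.
- Name in advance one set of pre-randomisation prognostic covariates for all models, for example age, four-frequency pure-tone average and Gold-MSI musical training.
- Show baseline balance descriptively by arm.
- Take credibility and expectation out of the list of variables that randomisation is expected to balance. Report them by arm and use them only in a labelled sensitivity analysis.

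All these variables are already collected, so the cost is revised wording and a few degrees of freedom. Site is left out of the suggested set on purpose. Its omission from the model is a separate decision under Modelling and inferential statistics, and this change need not reopen it.
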